### Outcomes

The outcomes are determined by change from baseline to six month follow-up. The primary outcome is change in power (Watt/kg) at the individual anaerobic threshold according to lactate kinetics during spiroergometry. Although the maximal oxygen uptake (VO_2−_peak) is currently the most popular risk stratification factor for patients with coronary heart disease, we decided to determine the individual anaerobic threshold as our primary outcome. It is well known that assessment of VO_2−_peak is limited by the ability of patients to engage in maximal exercising and influenced by their motivation and perceived exertion. Therefore, submaximal reference values of exercise capacity, like oxygen uptake at the ventilatory threshold (VT), have been demonstrated to be more objective [56]. Submaximal exercise values such as VT and ventilatory efficiency have been described as better predictors for mortality or major cardiac events than VO_2_-peak [57,58]. The concept of the lactate threshold for the determination of training loads is a method for endurance performance assessment and for the prescription of exercise intensities that is valid and reliable [59]. Particularly, individual anaerobic thresholds (IAT) determined by lactate kinetics in graded exercise treadmill protocols have been described to have an even higher test-retest reliability then the determination of the ventilator threshold [26].

More recently, a two-month residential rehabilitation program, including exercise training in patients with chronic heart failure, revealed that all exercise intensity related values at the IAT including VO_2_, VCO_2_, work rate in Watts, and VE were much more significantly improved than the respective values at maximal exertion [60]. We therefore decided to determine the IAT as main outcome variable in our intervention using a graded exercise protocol as developed by Dickhuth and co-workers [26] that is adjusted and validated for cycling [27].

Secondary outcomes are change in maximal aerobic capacity (VO_2−_peak); change in endothelial function according to the flow mediated dilatation; change in high-density lipoprotein levels; change in biomarkers of inflammation and oxidative burst; change in the waist-to-hip ratio and body mass index (BMI kg/m^2^) as determined by supervised medical anthropometry; change in the self-rated habitual physical activity according to the Habitual Physical Activity Questionnaire; change in quality of life according to the visual analog scale of the EQ-5D; change in the severity of impairment by angina symptoms according to the Seattle Angina Questionnaire; change in fatigue according to the Maastricht Questionnaire; change in quality of sleep according to the Jenkins Sleep Questionnaire; and change in illness perception according to specific items from the brief Illness Perception Questionnaire (item #1 ‘consequences score’; item # 3 ‘personal control’ and item # 6 ‘illness concern’). In a subgroup of participants, we will further be able to explore change in performance of goal planning according to the ToL.

Feasibility of the intervention will be assessed by analyzing procedures for recruitment (ratio of patients screened versus included), acceptability of allocation procedures and attrition rates (loss to follow-up measurements, completion rates) between the three conditions. Further, the dosage of PMT will be described by minutes and mode of intervention.

### Sample size calculation

As this is the first study on the effectiveness of a psychodynamic motivation and training program, we designed the study primarily to test the feasibility of PMT and possible effects that may be worth following up in a subsequent larger study. The sample size calculation was based on the following considerations: in general, exercise programs for patients with CHD yield increases in the aerobic capacity as determined by the VO_2_-peak of 2.6 ± 1.6 (mean ± standard deviation) versus 0.3 ± 1.4 mL/kg/min in the inactive control groups [61]. This difference corresponds to an effect size of about 1.5 standard deviations. With regard to change of the anaerobic threshold, a recent study on the effects of exercise training in patients with chronic heart failure found at the lactate threshold, a mean workload difference of 43 Watts with a standard deviation of about 17 Watts [60]. For our study we estimated a 50% lower effect size differences, as the exercise training was not supervised and therefore presumably less intensive.

Comparing PMT to EX and to TAU, while controlling the multiple type one error at a level of 0.05, each comparison has to be performed at the nominal level of 0.025 using the Bonferroni correction. With a sample size of n = 30 in each group, a standardized effect size of 0.82 can be detected at the two-sided level 0.025 with a power of 0.80. Assuming that the standard deviation of change in the individual anaerobic threshold is 17 Watts (which is roughly in accordance with results from [60]), this corresponds to an absolute effect of 14 Watts for PMT, which is less than half of the effect reported in [60].

### Randomization

The participants are randomized to three groups with n = 30 patients each. A computer program randomly assigned numbers from 1 to 90 to three sets representing the three groups. The numbers were hidden in closed envelopes. For each new participant an envelope was opened and the participant was allocated accordingly.

### Statistical methods

Categorical variables are presented as frequencies and percentages (n,%), continuous variables as means and standard deviations (mean ± standard deviation), or medians and quartiles for variables with skewed distributions (median (25th quartile, 75th quartile). Baseline characteristics of the three treatment groups will be compared with respect to age, sex, socioeconomic status, partnership, cardiovascular risk-factors (for example, smoking, obesity), comorbidity, variables characterizing patients with coronary heart disease (for example, medication) and outcome parameters.

Primary and secondary endpoints will be analyzed according to the intention-to-treat principle. Change from baseline to follow-up will be analyzed by analysis of covariance adjusting for baseline measurement of the respective outcome. Doing so, separate contrast are specified for comparing PMT with EX and TAU, respectively. Cohen‘s effect size will be calculated. In order to determine whether the effect of PMT is modified by presence of significant mental distress and psychosocial stressors at baseline, a test for interaction will be performed. Exposure to significant mental distress and psychosocial stressors will be defined by at least one of the following baseline criteria: PHQ-2 ≥ 2, GAD-2 ≥ 3, sleep disturbances (according to item #3 of the PHQ-9 ≥ ‘more than half the days’), and common psychosocial stressors according to the PHQ module (‘being bothered a lot’ by ‘difficulties with husband/wife, partner/lover or boyfriend/girlfriend’, or ‘stress of taking care of children, parents, or other family members’, or ‘stress at work outside of the home or at school’, or ‘having no one to turn to when you have a problem’). All analyses will be conducted on a two-sided level of significance with *P* < 0.05.

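### The two primary contrasts are sized at a Bonferroni level of 0.025, but the analysis section puts all analyses at 0.05; read literally, this gives a family-wise error of about 9% instead of the stated 5%

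*Protocol article*

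**What the plan says.** The Sample size calculation section treats PMT versus EX and PMT versus TAU as one family, "while controlling the multiple type one error at a level of 0.05". It concludes that "each comparison has to be performed at the nominal level of 0.025 using the Bonferroni correction". The sizing statement uses that level: with 30 patients per group, "a standardized effect size of 0.82 can be detected at the two-sided level 0.025 with a power of 0.80".

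The Statistical methods section sets out the analysis itself. It specifies an analysis of covariance of change, adjusted for the baseline value, in which "separate contrast are specified for comparing PMT with EX and TAU, respectively". These are the same two comparisons. The section mentions neither Bonferroni nor 0.025. Its last sentence reads "All analyses will be conducted on a two-sided level of significance with" P < 0.05, with no exception for the primary contrasts.

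**The concern.** Both sections are current text, and they give different thresholds for declaring PMT better on the primary outcome. The sample size section words its rule as a requirement on how the comparisons are carried out, so it is more than a planning device. The analysis section is where an analyst looks for the decision rule, and there the only level given is 0.05.

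Two things are at stake:

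- **The decision.** A primary contrast with P between 0.025 and 0.05 is positive under one section and negative under the other. If the choice stays open until the data are seen, the published protocol would support either answer.
- **The error rate.** The protocol claims 5% control over the two comparisons. Two tests at 0.05 each do not deliver that.

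**Working it through.** **Inputs.** From Sample size calculation: overall error 0.05; level per comparison 0.025, two-sided; standardized effect 0.82; power 0.80; SD of change 17 W; absolute effect 14 W. From Randomization: three groups of 30. From Statistical methods: two contrasts sharing the PMT arm, ANCOVA with one baseline covariate, all analyses at two-sided 0.05.

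**Step 1: reproduce the plan's own figures.**

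- Bonferroni split: 2 × 0.025 = 0.05.
- Absolute effect: 0.82 × 17 W = 13.9 W, which rounds to the stated 14 W.
- Power, two-sample t test with 58 df: noncentrality = 0.82 × √(30/2) = 3.18.

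| Two-sided level per contrast | Power at effect 0.82 | Effect detectable with power 0.80 |
|---|---|---|
| 0.025 | 0.807 | 0.814 |
| 0.05 | 0.878 | 0.736 |

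The stated pair (0.82, 0.80) reproduces at 0.025 and not at 0.05. The design was therefore built on the corrected level.

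**Step 2: family-wise error under each rule, when the three arms do not differ.**

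Each contrast has variance 2σ²/30. The two share the PMT mean, so their covariance is σ²/30 and their correlation is (σ²/30) / (2σ²/30) = 0.5. The chance of at least one false positive is

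1 − P(|Z₁| ≤ c and |Z₂| ≤ c), with correlation 0.5,

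where c = 1.96 for level 0.05 and c = 2.24 for level 0.025. This was checked by simulating one million null trials with a pooled variance on 90 − 3 − 1 = 86 df.

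| Rule for the two primary contrasts | Bivariate normal | Simulation | If independent | Upper bound |
|---|---|---|---|---|
| 0.05 each (Statistical methods, read literally) | 9.1% | 9.0% | 1 − 0.95² = 9.75% | 10% |
| 0.025 each (Sample size calculation) | 4.6% | 4.6% | 1 − 0.975² = 4.9% | 5% |

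If EX versus TAU (the third hypothesis under Objectives and hypotheses) were also tested at 0.05, the simulated figure for three contrasts would be 12.1%. This is only for context, because the 5% promise in the sample size section covers two contrasts.

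**Step 3: the range of results that the conflict affects.**

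The smallest observed difference reaching significance is t × √(2/30) SD, using an unadjusted two-sample t test with 58 df. That is about 0.52 SD at level 0.05 and 0.59 SD at level 0.025. With the plan's SD of 17 W, this is 0.52 × 17 ≈ 8.8 W and 0.59 × 17 ≈ 10.1 W. An observed difference between these two values would be classed differently by the two sections.

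**The case against.** The strongest reply is that the sections can be read together. The sample size section states a specific rule for exactly these two contrasts. The closing sentence of Statistical methods is generic and may only name the overall level, which is 0.05 in both places. With the correction carried over, the family-wise error is at most 5%. This reading is possible, so the 9% is conditional on following the analysis section literally. But the analysis section does not state the carry-over, and its closing sentence also covers the interaction test and the secondary endpoints, where 0.05 can only be a level per test.

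Other points on that side:

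- **Feasibility aim.** The sample size section says the study is designed mainly to test feasibility and look for effects worth pursuing in a larger study. A false positive would then chiefly prompt another trial, which limits the harm. The protocol nevertheless names one primary outcome, states effectiveness hypotheses and claims 5% control, so its analysis rule should match that claim.
- **PMT must beat both comparators.** The first hypothesis could be read this way, and two tests at 0.05 would then need no correction. The protocol does not state such a rule, and the sample size section chose the split.
- **Condensed article.** A fuller protocol or analysis plan may settle the matter. That would excuse a missing detail. It does not make two conflicting statements in the article consistent, and whoever writes the plan would still have to choose one.

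**Conclusion.** The contradiction is real and concerns the success criterion for the primary outcome. Followed as written, the analysis section gives a family-wise error of about 9.0%, nearly twice the 5% claimed; the level used for sizing gives 4.6%. These figures assume 30 analysed patients per arm, a common variance, no true difference between any arms, and success declared on either contrast. The sample size is not in question, since it reproduces at 0.025. The point should be settled before analysis because it decides what counts as a positive result.

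**What to change.** In Statistical methods, replace the blanket closing sentence with a rule stating that:

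- 0.05 is the family-wise level for the primary outcome, and PMT versus EX and PMT versus TAU are each tested at two-sided 0.025;
- unadjusted two-sided 0.05 applies only to the remaining analyses, which are labelled exploratory.

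Carrying the 0.025 across is enough to remove the contradiction. Holm's procedure is an acceptable alternative: the smaller P value is tested at 0.025 and, if that is significant, the other at 0.05. It holds the same 5% and never rejects less often than Bonferroni.

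The cost is one or two sentences before analysis. Group size stays at 30, and power at the stated effect stays at about 0.81 per contrast. Some primary P values between 0.025 and 0.05 would no longer count as positive: all of them under the plain split, and under Holm those where the other contrast has not passed 0.025. For the plain split, that is what the sample size section already commits to.

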### Ethical issues

The final study protocol and the final version of the written informed consent form were approved by the Ethics Committee of the Federal State of Rhineland Palatine in Germany (ref: 837.274.11.7816). The procedure set out in this protocol, pertaining to the conduct, evaluation, and documentation of this trial, were designed to ensure that all persons involved in the trial abide by the code of Good Clinical Practice and the ethical principles described in the current revision of the Declaration of Helsinki. The trial will be carried out in keeping with local legal and regulatory requirements. Before being admitted to the clinical trial, patients must consent to participate after the nature, scope, and possible consequences of the clinical trial have been explained in a form understandable to them. The patients must give written informed consent to participate in the study, including their consent to publish. Any findings during the study assessments that need further clarification are communicated to the patient by a letter with specific recommendations. For example, if there are clinically significant depressive symptoms, the patient will be informed about this finding with the recommendation to consult his general practitioner for further diagnostic evaluation and treatment. The participating patients are paid an allowance of €25 for baseline assessment and €75 for the follow-up assessment.

## Discussion

According to our knowledge, this is the first study investigating effects of psychodynamic psychotherapy on cardiorespiratory and physical fitness. We hope that the study will yield knowledge about the optimal dosage of intervention an individual patient needs, respectively which patients profit from such individualized treatment approaches, and for who personalized exercise advice or even treatment as usual might be sufficient. As this study focused primarily on motivational barriers for lifestyle improvement, no supervised exercise training was applied. Home based exercise training was considered as the appropriate mode, as this keeps the threshold for participation lower as opposed to structured supervised exercise training with regular schedules. Important strengths of the study are the use of biological outcome parameters. Changes in the individual anaerobic lactate threshold and oxygen consumption are much more reliable measures of improved physical activity than self-reported increases in physical activity. Further, by analyzing change of endothelial function we will be able to describe effects on an important surrogate parameter of cardiovascular disease.

A major limitation of the study is the short duration of observation. The investigation of the sustainability of exercise and life style compliance needs at least one or more years of observation. Another important limitation concerns the recruitment of participants. As the participants need to give their informed consent to participate in this trial, we expect that the vast majority of the patients are already at the stage of contemplation about the necessity to improve their physical activity. This is to say, we will not be able to recruit pre-contemplative patients [62,63]. These latter pre-contemplative patients, however, will presumably have the most severe lifestyle problems as they are even not emotionally aware of the detrimental consequences of their behavior. These patients actually represent a target population of our psychodynamic approach, as psychotherapy especially helps to build up motivation, for example, by helping to experience emotionally the costs of one’s maladaptive behavior. Due to this selection-bias, inferences from our study to pre-contemplative patients will be restricted. Trial designs have to be developed that enable both informed consent and inclusion of ‘unwilling’ patients. Further limitations comprise the lack of a more elaborated assessment of blood pressure (for example, home or ambulatory blood pressure measurements at regular intervals). Due to this lack, the analysis of effects on high blood pressure is limited. However, blood pressure at baseline and follow-up will be considered as a potential confounder of the endpoints. If adequate, additional adjustment for blood pressure will be applied. Another limitation is the lack of the assessment of endothelium-independent vasodilatation [64-66]. However, a number of studies showed no effect of exercise on nitroglycerin (endothelium-independent) responses, at least in the forearm circulation, and that these responses were not associated with VO_2−_peak levels [67]. Last but not least, differences in the initiation of psychopharmacotherapy may constitute a potential bias regarding secondary endpoints such as fatigue and quality of life. In order to be able to control for this potential bias, the rate of psychopharmacotherapy will be assessed at baseline (current) and at follow-up (past, current).

## Trial status

Recruitment of participants is ongoing. The first participant was included in October 2011. We expect that the last patient will have finished by May 2014.

## Abbreviations

BMI: Body mass index; CCS: Severity of angina according to the Canadian Cardiovascular Society; CHD: Coronary heart disease; CRF: Cardiovascular risk-factors; ECG: Electrocardiography; EX: Advice in exercise training; FMD: Flow-mediated dilation; GAD-2: Two-item anxiety version of the GAD-7; GAD-7: Generalized anxiety disorder scale; HDL: High-density lipoprotein; HPAQ: Habitual physical activity questionnaire; IAT: Individual anaerobic threshold; IPQ: Brief illness perception questionnaire; LDL: Low-density lipoprotein; L-FMC: Flow-mediated constriction; MFI: Multidimensional fatigue inventory; NYHA: Symptoms of heart failure according to the New York Heart Association; PCI: Percutaneous coronary intervention; PHQ: Patient health questionnaire; PHQ-2: Two-item depression module of the PHQ; PMT: Psychodynamic motivation and training program; SAQ: Seattle Angina questionnaire; TAU: Treatment as usual; ToL: Tower of London; VE: Minute ventilation; VO2-peak: Maximal oxygen uptake; VT: Ventilatory threshold; WHR: Waist-to-hip ratio
